#### Control condition

Treatment as usual will be provided as optimized care as usual. Participants will be offered four face-to-face sessions with the mental health counselor at the general practice. The treatment follows the guideline for anxiety complaints as developed by the Dutch College of General Practitioners. This guideline prescribes psycho-education and, if necessary, short-term CBT or problem-solving therapy. A manual for the treatment older adults with anxiety complaints has been developed by the researchers. The manual comprises 12 small interventions. Each intervention focuses on either a common form of anxiety (worrying, panic symptoms, social anxiety), cognitive or behavioral aspects typical of most anxiety complaints (catastrophic thinking, avoidance), or consequences of anxiety (sleeping problems, physical tension). All interventions consist of psycho-educative texts and exercises based on CBT. During the first session, the mental health counselor and participant make an overview of the psychological complaints of the participant. Based on this inventory, one or more of the small interventions are selected to form the basis of the next three sessions. In order to prevent treatment diffusion, the delivery of interventions resembling the web-based interventions (i.e. eHealth interventions in general and ACT and mindfulness-based interventions in particular) are not allowed. Mental health counselors will complete a short online questionnaire that measures treatment protocol adherence after every session. Mental health counselors in this condition will follow a training from an experienced clinical psychologist, to practice with the protocol. They will also be supervised during the study.

### Assessments

Table 1 depicts an overview of the assessment instruments that will be used throughout the study. All questionnaires—except for the M.I.N.I.-Plus and SDS—will be conducted online. The M.I.N.I.-Plus and SDS are conducted by telephone.

**Table 1 Tab1:** Overview of assessments during the study

Assessment	Screening	T0 Baseline	During intervention	T1 Post-intervention (14 weeks after T0)	T2 Follow-up (26 weeks after T0)	T3 Follow-up (52 weeks after T0)
GAD-7	X	X	–	X	X	X
PHQ-9	X	X	–	X	X	X
PHQ-4 (GAD-2 + PHQ-2)	–	–	X	–	–	
M.I.N.I.-Plus	X	–	–	X	–	X
SDS	X	–	–	X	–	X
CERQ	–	X	–	X	X	X
AAQ-II	–	X	–	X	X	X
MHC-SF	–	X	–	X	X	X
FFMQ-SF	–	X	–	X	X	X
EQ-5D-5 L	–	X	–	X	X	X
TIC-P	–	X	–	–	X	X
CSQ-8	–	–	–	X	–	–
Self-esteem,Mastery andSupport	–	X	–	–	–	–
Life events	–	X	–	–	–	–
Somatic problems	–	X	–	–	–	–
Demographics and other information	–	X	–	–	–	–
Treatment credibility and expectancy	–	–	X	–	–	–
Emotion regulation	–	X	X	X	X	X
Behavioral avoidance	–	X	X	X	X	X
Treatment expectancy	–	–	X	–	–	–
Self-efficacy	–	–	X	–	–	–
SRS	–	–	X	–	–	–

*GAD-7* General Anxiety Disorder 7, *PHQ-9* Patient Health Questionnaire 9, *PHQ-4* Patient Health Questionnaire 4,*GAD-2* General Anxiety Disorder 2, *PHQ-2* Patient Health Questionnaire 2, *M.I.N.I.-PLUS*, Mini-International Neuropsychiatric Interview-PLUS, *SDS* Sheehan Disability Scale, *CERQ* Cognitive Emotion Regulation Questionnaire, *AAQ-II* Acceptance and Action Questionnaire II, *MHC-SF* Mental Health Continuum Short Form, *FFMQ-SF* Five Facet Mindfulness Questionnaire Short Form, *EQ-5D-5 L* EuroQol 5 dimensions 5 levels questionnaire, *TiC-P* Trimbos/iMTA questionnaire for Costs associated with Psychiatric Illness, *CSQ-8* Client Satisfaction Questionnaire 8, *SRS* Session Rating Scale

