Each participant will complete four main measurements during the study: before the start of the intervention (and before participants are informed about which intervention they will receive) (T0); directly following the intervention (three months after baseline; T1); and six (T2) and twelve months (T3) after baseline. All measurements consist mainly of online self-report questionnaires. T0, T1, and T3 also include a telephone interview conducted by a research assistant. The research assistant that conducts the telephone interviews will be unaware of treatment allocation of the participants. If for any reason this blinding is broken, another research assistant (that is blind to treatment condition of the participant) will take over the telephonic assessment.

Figure 1 shows the flow chart of the study design. The SPIRIT Checklist and Figure are presented as Additional file 1 and 2 respectively. The study is approved by the medical ethical committee of the Leiden University Medical Center (LUMC; no. P16.248).

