### Sample size

Cluster randomization will be applied at the level of the participating mental health counselors. Assuming a mean cluster size of five patients per counselor, an intraclass correlation coefficient of 0.01 [52] and a coefficient of variation of 0.30 [53], 18 mental health counselors in each intervention arm and 90 participants per study arm are needed to detect a between group difference on the GAD-7 with a medium effect size (d = 0.45) with an alpha of 0.05 (two-tailed) and a power of 0.80. Compensating for an anticipated dropout of 25% (based on trials similar to the proposed study with regard to either the treatment approach [40, 54] or the study population [26]), 240 participants will have to be included at baseline. The endpoint for this sample size is 14 weeks. In the most recent and comprehensive Cochrane meta-analysis of 101 studies of media-delivered CBT for anxiety disorders in adults, moderate-quality evidence showed medium effect sizes for CBT compared to control conditions (d = 0.67; 95% confidence interval = 0.55–0.80) [23]. These effects were somewhat smaller than those reported in other recent reviews [17, 19–22] and also smaller than the large effect sizes for Internet-based ACT (0.80 and 0.87) in the study of Fledderus et al. [40] and for Internet-based CBT for anxiety complaints in older adults (1.43) in the study of Dear et al. [26]. These last two studies both compared active treatment to a waiting list control condition. Furthermore, Pots et al. reported an effect size of 0.41 for web-based ACT (with e-mail support) compared to an active control group (expressive writing) [41]. Based on these studies, a moderate effect size of d = 0.45 is estimated for the difference between the ACT online intervention and treatment-as-usual.

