
#### Procedure during study participation

During the intervention, participants will fill in a short questionnaire assessing potential mediator variables several times. At these moments they will also complete the GAD-2 [55] and PHQ-2 [56] to measure respectively anxiety and depression symptoms (the combination of PHQ-2 and GAD-2 is also known as the PHQ-4 [57]). They will also be asked whether they have had recurrent thoughts about death or hurting themselves in the past week, using an item of the PHQ-9 [49]. When participants have had suicidal thoughts in the past week, they will be recommended to discuss this with their mental health counselor at the general practice. Furthermore, their mental health counselor will be notified about the presence of suicidal thoughts by the researchers and are asked to contact the participant. Participants in the experimental condition complete this questionnaire at the end of every online lesson (nine times in total). Participants in the control condition, receive an email with a link to this questionnaire after every session with the mental health counselor (a total of four times).

Both interventions are delivered in a timespan of maximum 12 weeks, after which participants receive an e-mail with a link to the online self-report questionnaires of the post-treatment assessment (T1). T1 also includes a clinical interview by telephone conducted by a research assistant. The follow-up assessments take place six (T2) and twelve months (T3) after baseline. Both these assessments consist of self-report questionnaires and T3 also includes a clinical telephone interview. Figure 1 shows an overview of the patient flow through the phases of the study.

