#### Prevention of attrition

Although available research shows that the effect of eHealth interventions does not depend on age and that older adults are even more adherent than younger adults [58], several precautions will be taken to reduce dropout and heighten compliance throughout this study. If participants fail to complete study assessments or intervention assessments, motivational reminders will be send repeatedly by email. Furthermore, individuals who complete all study assessments will take part in a lottery for gift vouchers worth €50, in order to stimulate them to complete all study assessments (lotteries will take place every year during the data collection period). If participants drop out or stop using the intervention, they will be asked for the reason(s) why they decided to quit the intervention and/or study.

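### The primary GAD-7 has only an online route at T1, although a blinded telephone interview at the same assessment could collect it when the web form is not returned

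*Protocol article*

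**What the plan says.** All references are to the protocol article.

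- **Mode of collection (Assessments).** "All questionnaires—except for the M.I.N.I.-Plus and SDS—will be conducted online". The next sentence adds: "The M.I.N.I.-Plus and SDS are conducted by telephone". The GAD-7 is thus online.
- **Primary endpoint (Primary outcome).** The endpoint is the GAD-7 at T1, 14 weeks after baseline. The same section cites reliability and validity evidence for a web-based Dutch version.
- **Delivery (Procedure during study participation).** After the intervention period, participants are e-mailed a link to the T1 questionnaires.
- **Pursuit of non-responders (Prevention of attrition).** "If participants fail to complete study assessments or intervention assessments, motivational reminders will be send repeatedly by email". The section also describes a voucher lottery, and says that people who drop out will be asked why, without naming a mode of contact.
- **The telephone call (Design).** "T0, T1, and T3 also include a telephone interview conducted by a research assistant". The assistant is unaware of allocation and is replaced if blinding is broken. Functional impairment confirms that the SDS is asked by telephone at T1 and T3. Telephone numbers are taken at screening (Recruitment of participants).
- **Expected loss (Sample size).** Dropout of 25% is allowed for, giving 240 enrolled, with 14 weeks as the endpoint.

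**The concern.** At T1 two channels reach the same participant. The web channel carries the primary outcome, and the telephone channel carries two secondary instruments. The article describes no crossover between them. A participant who ignores the link but answers the telephone contributes a diagnosis and a disability score, but no value for the outcome on which the trial is sized and judged.

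Statistical analysis promises intention-to-treat analyses, with mixed models and model-based imputation for missing data. These methods work well if missingness depends only on what has been observed, but they do not restore the outcome. Where a score can be obtained on a call that is taking place anyway, obtaining it is better than modelling it.

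**Working it through.** **1. Inputs.** From Sample size: d = 0.45, two-sided alpha 0.05, power 0.80, mean cluster size 5, ICC 0.01, coefficient of variation 0.30 (taken here as that of cluster size, an assumption), 18 counselors and 90 participants per arm, dropout 25%, 240 enrolled.

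**2. The plan's own figure.**
- Individually randomized n per arm: 2 × ((1.960 + 0.842)/0.45)² = 77.5, so 78.
- Design effect: 1 + ((0.30² + 1) × 5 − 1) × 0.01 = 1.0445.
- The normal approximation needs only 78 × 1.0445 = 81.5, so 82 per arm.
- A t-test on cluster degrees of freedom, 2(k − 1), gives power 0.795 with 17 counselors per arm (85 participants) and 0.818 with 18 (90 participants, 34 df). Eighteen is the smallest number that reaches 0.80, so the stated 90 per arm is reproduced.
- Dropout: 180/0.75 = 240, also reproduced.

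**3. What is at stake.** 0.25 × 240 = 60 primary scores. This is an upper limit for recovery, because dropout includes people who would refuse the call as well.

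**4. What recovery would add.** The recovery share is not in the documents, so the shares below are assumptions. Power uses 34 df, with the design effect recomputed for the larger clusters.

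| Share of the 60 recovered | Scores recovered | Missing | Evaluable per arm | Design effect | Power |
|---|---|---|---|---|---|
| 0 | 0 | 25% | 90 | 1.0445 | 0.818 |
| 1/5 | 12 | 20% | 96 | 1.0481 | 0.841 |
| 2/5 | 24 | 15% | 102 | 1.0518 | 0.861 |

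Each 12 scores add about two percentage points. Power is above 0.80 in every row, including the first.

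**5. Bias.** Let pA and pC be the proportions missing in the ACT and control arms. Let δ be the amount, in SD, by which missing patients are worse than the model predicts, equal in both arms. The shift in the contrast is (pA − pC) × δ.
- Equal loss, 25% and 25%: the shift is 0 whatever the common δ.
- Illustration, with assumptions not in the documents: 30% against 20% and δ = 0.5 gives 0.10 × 0.5 = 0.05 SD. Reversing the split reverses the sign.

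The documents give no basis for choosing among these cases.

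**The case against.** **Online collection has a stated basis.** The cited Dutch validation is of the web version, and screening and baseline GAD-7 are also online, so mode is constant from baseline to endpoint. A telephone score changes the mode precisely among non-responders. This stands as a real cost of the fix. It is a reason to restrict the telephone to people still missing after reminders and to record the mode.

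**Pursuit by e-mail alone is read from silence.** The article excludes no other contact, and a fuller protocol may describe some. That is fair for reminders, and the point should be read as the only pursuit described. It does not reach the mode of the GAD-7, which Assessments fixes explicitly.

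**The loss is already budgeted.** This stands in full: no power failure is shown.

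**A stronger reading is tempting.** A reader might infer that loss must be heavier in the ACT arm, because its treatment is a web course, and that the contrast is therefore biased. The documents do not support this:
- The ACT arm also has four face-to-face counselor sessions, the same number as control.
- The T1 link is e-mailed separately from the course.
- During treatment it is the control participants who receive e-mailed questionnaire links, while ACT participants answer at the end of each lesson.
- Everyone must have Internet access and completes screening and baseline questionnaires online.

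A reader might also infer that the lottery, open only to people who complete every assessment, harms later retention. Nothing in the documents shows that it does.

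**Conclusion.** The point holds as avoidable missing data in the primary outcome. The article provides no telephone route for the GAD-7 at an assessment where a blinded telephone contact is already planned. At most 60 of 240 scores are concerned. The recoverable number is unknown and depends on how many web non-responders would take the call.

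The design is not underpowered at the planned loss. Bias would arise only if loss, or the unexplained gap between missing and observed patients, differed between arms and the data were not missing at random. With equal loss and an equal gap it is zero. The case for change rests on the low cost of obtaining the scores, not on any demonstrated distortion. It is an inexpensive improvement worth making and does not threaten the trial's validity as planned.

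**What to change.** In Assessments and Prevention of attrition, state the following:

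1. If the online GAD-7 is still missing after the e-mail reminders, the blinded research assistant asks its seven items during the T1 (or T3) interview already planned. The trigger must follow the reminders, so that people who would answer online are not moved to the telephone.
2. The interview is scheduled within the assessment window. The GAD-7 asks about the last two weeks, so a late call measures a later state.
3. The rule applies identically in both arms and regardless of whether treatment was stopped.
4. Mode of completion is recorded, and a sensitivity analysis is run on web-completed scores only.

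**Cost.** Seven items on an existing call, one mode variable and a minor amendment, with no extra staff or visits.

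**Limits.** A web-versus-telephone mode effect is possible in a minority of scores. The web-only analysis shows whether the result depends on the telephone scores, but it brings back the original missing data, so it cannot separate mode from non-response. No telephone interview is planned at T2, so the rule does not help there.

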### Primary outcome

#### Anxiety symptom severity

The primary outcome—severity of anxiety symptoms—will be assessed with the GAD-7 [48]. This questionnaire will be used to screen participants on anxiety symptoms and to measure change in these symptoms from baseline to post- and follow-up tests. The primary endpoint for this measure is the measurement 14 weeks after baseline (T1). The GAD-7 consists of seven items that are rated on a 4-point scale ranging from 0 (not at all) to 3 (nearly every day), e.g. “Over the last 2 weeks, how often have you been bothered by: feeling nervous, anxious or on edge.” Higher scores indicate more anxiety symptoms. Total scores are in the range of 0–21 and scores of 5, 10, and 15 are taken as the cut-off points for mild, moderate, and severe anxiety. Psychometric properties of the GAD-7 are adequate and the scale may also be used as a screener for panic disorder, social anxiety, and post-traumatic stress disorder [48, 55, 62]. The reliability and validity of a web-based Dutch translation of the GAD-7 have also been established [63].

Furthermore, during treatment, participants will fill in the GAD-2 [55] several times to measure anxiety symptom severity. The GAD-2 consists of the first two items of the GAD-7, which reflect core anxiety symptoms (“Feeling nervous, anxious, or on edge” and “Not being able to stop or control worrying”). Scores on the GAD-2 will be used in the mediation analyses. The GAD-2 is a reliable, valid, and sufficiently sensitive and specific instrument [55, 63, 64].

### Secondary outcomes

#### Depression symptom severity

Depression symptoms will be measured with the PHQ-9 [49]. This questionnaire will be used as a screener for depressive symptoms and to measure change in depressive symptomology from baseline to post- and follow-up tests. The questionnaire consists of nine items and includes the DSM-IV criteria for a major depressive disorder. The items are rated on a 4-point scale ranging from 0 (not at all) to 3 (nearly every day). Scores are in the range of 0–27 and cut-off points of 5, 10, 15, and 20 represent mild, moderate, moderately severe, and severe levels of depressive symptoms. The PHQ-9 is sensitive to change, has good sensitivity and specificity for detecting depressive disorders, and its psychometric properties are adequate [62, 64, 65]. In addition, depression symptoms will be measured with the PHQ-2 [56] at several times during treatment. The two items of the PHQ-2 (which correspond to the first two items of the PHQ-9) measure core depressive symptomology. The scores on these items will be used in the mediation analyses. The reliability, validity, and sensitivity to change of the PHQ-2 have been established [56, 57, 64].

#### Presence of psychiatric disorder

Presence of current and/or lifetime diagnosis of anxiety disorder (generalized anxiety disorder, panic disorder, agoraphobia, specific phobia, social phobia), obsessive-compulsive disorder, depressive disorder, post-traumatic stress disorder, and illness anxiety disorder will be determined by the M.I.N.I.-Plus [51]. Current substance abuse disorder and suicide risk as well as a lifetime diagnosis of psychotic disorder and bipolar disorder will also be assessed. The M.I.N.I.-Plus is the most widely used psychiatric structured diagnostic interview instrument in the world and has been validated against the Structured Clinical Interview for DSM diagnoses (SCID-P) and the Composite International Diagnostic Interview for ICD-10 (CIDI) [51]. Trained research assistants who are blind to the randomization scheme will conduct the M.I.N.I-Plus by phone. The M.I.N.I.-Plus will be administered during the screening (T0). At T1 and T3, only the modules for current anxiety disorders, depressive disorder, post-traumatic stress disorder, obsessive-compulsive disorder, and illness anxiety will be conducted. Minor adjustments will be made to the M.I.N.I.-Plus, so it corresponds with the criteria of the DSM-V. When uncertain of a diagnosis, the interviewers will have the opportunity to consult a psychiatrist or senior clinical psychologist, who is also blind to randomization status of the participants.

#### Functional impairment

The SDS [50] was developed to assess functional impairment in three inter-related domains: work/school; social life; and family life. The SDS measures the extent to which work/school, social life, and home life or family responsibilities are impaired by psychiatric symptoms on a 10-point visual analogue scale. The three items can be summed into a single dimensional measure of global functional impairment that ranges from 0 (unimpaired) to 30 (highly impaired). A psychometric analysis in a large sample of primary care patients demonstrated that the SDS has good psychometric qualities [50]. Research assistants that are blind to group allocation, will administer the SDS by telephone during the screening (T0) and at T1 and T3.

#### Cognitive emotion regulation

The subscales Rumination, Catastrophizing, Positive reappraisal, and Blaming yourself of the CERQ [66, 67] will be used to measure the extent to which participants use these cognitive coping strategies when confronted with adversities. The choice for these subscales is based on several studies that have demonstrated the association between these strategies and anxiety and depression symptoms [67–69]. The subscales consist of four items each. Higher scores on a subscale indicate that this cognitive coping strategy is more often used to regulate emotions. Psychometric properties of the Dutch CERQ are adequate [68, 70].

#### Experiential avoidance

The Acceptance and Action Questionnaire (AAQ-II) [71, 72] is a uni-dimensional measure [72, 73] that assesses experiential avoidance: the unwillingness to remain in contact with aversive private experience and behaviors aimed at altering these experiences or the events that elicit them. The AAQ-II originally contained ten items, but a study showed that a seven-item version has better psychometric qualities [72]. Items are scored on a 7-point scale ranging from 1 (never true) to 7 (always true). Higher scores reflect higher levels of experiential avoidance. The reliability and validity of a Dutch translation of the AAQ-II has been established in a sample of moderately depressed and anxious individuals [73].

#### Positive mental health

The Mental Health Continuum-Short Form (MHC-SF) [74] is a 14-item self-report questionnaire for positive mental health assessment. The questionnaire consists of three subscales, corresponding with the three dimensions of positive mental health: three items for emotional wellbeing; six items for psychological wellbeing; and five items for social wellbeing. Items are rated on a 6-point scale ranging from 0 (never) to 5 (every day). Confirmatory factor analysis (CFA) confirmed the three-factor structure of a Dutch translation of the MHC-SF. Results from the same psychometric study also revealed high internal and moderate test–retest reliability for the Dutch MHC-SF [74].

